## Abstract

**Background:**

Antimicrobial resistance (AMR) is recognized as a global concern, with particularly severe consequences in low- and middle-income countries. Although it may occur naturally, it is also an anthropogenic problem linked to the irrational use of antibiotics in humans and animal husbandry and the use of pesticides in plant agriculture. Generally, data on AMR and evidence of effective and feasible multifaceted interventions are limited in many African countries.

**Objective:**

This study aims at (1) assessing baseline data on AMR pathogens in Burkina Faso and Ghana; (2) understanding perceptions and quantifying use of antibiotics among health care workers, communities, and livestock farmers; and (3) defining and refining an AMR intervention using a design thinking approach.

**Methods:**

This multidisciplinary study will be conducted in two rural districts and will consist of two phases. First, baseline data will be collected on AMR pathogens along dominant food production chains. extended-spectrum beta-lactamase (ESBL)–producing Escherichia coli and Klebsiella pneumoniae will be selected as indicator mechanisms for AMR because of their high occurrence among animals and humans. The perception and understanding of AMR and antibiotic use among different stakeholders and community members will be assessed using epidemiologic and socio-anthropological methods. Qualitative methods will include participant observations, in-depth and key informant interviews, and focus group discussions. The quantitative part will consist of the development of an inventory of circulating antibiotics and a household survey. Second, key informant and in-depth interviews will be conducted with One Health stakeholders in preparation for the intervention development. Subsequently, multidisciplinary “design teams” will develop ideas for an intervention on AMR using a design thinking approach.

**Results:**

Data collection started in April 2022. The analysis of microbiological, anthropological, and socio-epidemiological data is ongoing in both countries. The intervention development has been initiated in Ghana but has not started yet in Burkina Faso. All results are planned to be submitted to peer-reviewed journals by December 2025. First, manuscripts will be published for each discipline. Afterward, the results of the 3 disciplines will be combined in multidisciplinary papers, and a publication of the evaluation of the intervention will follow.

**Conclusions:**

Owing to the multifactorial nature of AMR, different perspectives need to be considered to develop a holistic context-based intervention that is tailored to local needs. This study stands out in its combination of different disciplinary and epistemological perspectives following the One Health paradigm and taking a design thinking approach to develop an intervention. Thereby, collaboration across disciplines and social levels and a participatory bottom-up approach will be promoted to achieve a common understanding of problems and needs and to develop an accepted and efficacious intervention. The national AMR networks and policymakers will be continuously involved in the project.

**International Registered Report Identifier (IRRID):**

DERR1-10.2196/66424

## Introduction

### Overview

Antimicrobial resistance (AMR) is rising to dangerously high levels in all parts of the world and presents a threat to public health, food security, and (economic) development [1]. Currently, AMR is presented as being responsible for 700,000 deaths per year and could result in 10 million annual deaths per year by 2050 if no action is taken [1]. As new resistance mechanisms are emerging and spreading globally, the ability to treat common infectious diseases and enable chemotherapies, operations, and many other activities is threatened [2,3]. It is acknowledged as an urgent global problem that concerns every country irrespective of its level of income and development, but effects are hypothesized to be even more significant in low- and middle-income countries (LMIC) [1,4]. In social sciences, however, experts highlight how AMR can be exploited for political ends [5], the invisibility of several causes of AMR [6], and significant scientific knowledge gaps on this subject [7]. Legido-Quigley et al [8] described AMR as a “wicked problem,” as it encompasses complex networks of different stakeholders with incompatible interests.

AMR is spread via diverse agents including humans, animals, alimentation, soil, and water. Although resistance can emerge naturally through evolutionary processes [9,10], it can also occur through anthropogenic pressure resulting from an overreliance on antibiotics. Infections in humans and animals caused by extended-spectrum beta-lactamase (ESBL)–producing *Escherichia coli* and *Klebsiella pneumoniae* are increasingly resistant to most antibiotics globally due to their high diversity and rapid mutation [11,12]. The evaluation of these two gram-negative bacteria could serve as an important indicator for the prevalence of AMR in local settings.

It is critical to recognize how human practices interact with natural microbial ecology in compounding AMR risks. Within the human health sector, the reliance on broad-spectrum antibiotics, especially in the absence of diagnostics, has been identified as a major contributor to the emergence of AMR [13]. The widespread use of antibiotics in livestock exceeds direct human consumption and is driven by economic imperatives to maximize production, prevent disease, and enhance growth [7,14,15]. As most of these antibiotics are not fully metabolized but released into the environment as waste products, misguided antibiotic use has a concurrent ecological impact by affecting wild bacteria populations and promoting further antibiotic resistance development [16]. This highlights the ecological consequences of antibiotic misuse and the entangled nature of environmental, agricultural, and health systems. Additionally, the soil contains microorganisms with naturally occurring genes that can facilitate the development of AMR in the natural environment [3,7].

The relevance of this research project is multifaceted: First, the availability of information on AMR in Africa is limited. This stems from weak laboratory and surveillance systems and processes, where only a small fraction of facilities conducts bacteriological testing and the microbiological data that do exist are often of poor quality [4,17,18]. Similarly, more data on antibiotic consumption and access to health care in animal and human health are needed [19]. In addition, a One Health approach should be implemented in future studies to develop efficient interventions on AMR and improve AMR surveillance and control in Africa [19,20]. Second, the rates of AMR are higher in certain LMIC, while individual antibiotic consumption is lower in comparison with high-income countries, indicating that other factors are influencing the prevalence of AMR [9]. Third, the effects of AMR on various societal sectors, including health and economic consequences, risk being more significant in African countries due to predominant livelihoods and living conditions [21,22]. In recent years, the use of antibiotics in LMIC has increased substantially both for humans and animals because of economic growth and changes in diet [23]. At the same time, antibiotic policies concerning manufacture, dispensation, and prescription in many LMIC are often missing or lacking regulatory enforcement due to socioeconomic challenges, large population size, and challenged health care systems [24]. Fourth, the current body of literature “has created little clarity about what interventions are best suited to achieve AMR goals across contexts, cultures and health systems” [25]. The need to act on AMR at a global level is well-known and agreed upon; however, an implementation gap of action and interventions can be observed [26]. Evidence of effective and feasible multifaceted interventions in sub-Saharan African countries is limited, and studies show that challenges for implementation of interventions are numerous. Nevertheless, several initiatives at international and local levels have demonstrated that effective interventions are feasible in LMIC and that contextualization is essential [27].

### Study Objectives

This paper presents the study protocol for a multidisciplinary research project on AMR in 2 districts of Burkina Faso and Ghana using a One Health perspective and design thinking approach. The study has the following aims: (1) assessing baseline data on AMR pathogens along the food chain in the Kossi Province, Burkina Faso, and the Asante Akim North District, Ghana; (2) understanding and quantifying perceptions and use of antibiotics among health care workers, communities, and livestock farmers as well as defining patterns of access and utilization of antibiotics; and (3) defining and refining an intervention aimed at reducing the impact of AMR and improving the way this issue is addressed using a stakeholder-driven approach.

## Methods

### Study Setting

The research project will be conducted in Burkina Faso and Ghana, both located in the West African subregion. The research site in Burkina Faso is the rural Kossi Province, located in the northwest of the country and corresponding to the Nouna Health District. The population is mostly living in the semi-urban town Nouna, representing the administrative center of the province [28]. Nouna Health District has a population size of about 320,232 inhabitants and a surface area of 7464 km^2^ [28]. The main economic activities are farming and animal breeding [29]. A Health and Demographic Surveillance System has been established in the province and is managed by the Centre de Recherche en santé de Nouna (CRSN; Nouna Health Research Center). Burkina Faso has a national human and animal surveillance system for AMR consisting of 15 designated laboratories since 2018 and is enrolled in the Global Antimicrobial Resistance and Use Surveillance System (GLASS) of the World Health Organization (WHO) but is not yet reporting data to the system [30]. Burkina Faso’s National Action Plan (NAP) was published in 2018 but has not been implemented by the government yet [30].

The research site in Ghana is in the semi-urban and rural Asante Akim North District, which is in the eastern part of the Ashanti Region. The district has a size of 1218 km^2^ and approximately 85,788 inhabitants [31]. Approximately 72% of the district’s work force is employed in the agrarian sector [32]. Multiple health institutions are serving in the district and are constituted by private sector actors, religious missions, and public sector actors [32]. Ghana is enrolled in the WHO GLASS. However, there is no precise nationwide surveillance system on antimicrobial use and AMR prevalence, and no data were contributed in 2020 and 2021 [33-36]. The establishment of a nationwide AMR surveillance system is outlined in the NAP but has yet to be implemented [36,37]. Ghana is considered a leading country on the African continent for handling AMR due to its work and approach including the establishment, in 2011, of the Ghana National Policy Platform on AMR, which consists of various stakeholders from diverse institutions and sectors, thereby integrating the One Health approach [36]. Moreover, the NAP on AMR (2017-2021) and a policy document on antimicrobial use and resistance were officially launched in April 2018 in the country [36,38]. However, policy and project implementation is lagging due to poor coordination of the different stakeholders, insufficient financial resources and infrastructure, and enforcement of regulations [36].

Ghana and Burkina Faso are neighboring countries but different in many respects, such as the socioeconomic level, the structure of the health system, the presence of industries, and national security. Therefore, it would be of interest to contrast the information collected between the two study sites and to see the influence of these factors on AMR and what this could mean for possible interventions. In addition, through the development of a south-south collaboration between the two countries, knowledge can be shared, and synergy effects can be used for a holistic approach to AMR.

### Study Design

#### Overview

This research project consists of 2 phases (Figure 1). Phase 1 consists of multidisciplinary research on AMR, looking at it from different perspectives, namely, microbiology, anthropology, and socioepidemiology. This will consist of baseline data collection on AMR pathogens (ie, microbiology [1.1.]) We will explore perceptions and use of antibiotics among health care workers, communities, subsistence and semi-intensive livestock farmers, and institutional actors (ie, anthropology [1.2.] and socioepidemiology [1.3.]). Thereby, we are following an exploratory sequential mixed methods design by initially using qualitative methods to then develop quantitative tools in the next step. In the second phase, we will use a design thinking approach to develop a targeted intervention in collaboration with different stakeholders to improve the way of addressing the issue of AMR (ie, interventional research component [2.]). The identified stakeholders will be involved from the beginning of the project, with their opinions and perceptions of the problem and suggested solutions prioritized in the design thinking process.

**Figure 1 figure1:**
[figure not shown]
Research design: triangulation between 3 disciplines to develop an intervention using a design thinking approach. AMR: antimicrobial resistance.

#### Phase 1.1: Microbiology

First, we will assess baseline data on AMR pathogens along the dominant food chains: poultry in Ghana and poultry and beef in Burkina Faso. ESBL-producing *E. coli* and *K. pneumoniae* will be selected as the indicator mechanisms due to their high prevalence among animals and humans. Farms will be included in the sample if their poultry or cattle are sent to the local abattoir and sold in sampled local markets and retail shops. Due to local practices, the AMR prevalence will also be tested among free-range, so-called backyard, chickens in the villages.

A total of 1500 fecal samples will be collected from poultry, along with 500 meat samples from markets, 200 from retail shops, and 100 from abattoirs. During each sampling visit, individual fecal droppings from broilers (on poultry farms) or cattle (on farms) will be collected in sterile containers. These samples will then be placed in a transport box maintained at 2 °C to 4 °C to ensure proper preservation. In markets, retail shops, and the abattoir, meat samples of approximately 1 gram each will be collected into a sterile plastic bag and transported on ice to the Kumasi Centre for Collaborative Research in Tropical Medicine laboratory in Kumasi. In a biosafety cabinet, the samples will be transferred into sterile disposable petri dishes, and the meat will be diced into smaller pieces with a sterile surgical blade and transferred into Brain Heart Infusion (Oxoid) broth. After incubation at 37 °C for 18 hours to 24 hours in normal atmosphere, the broth will be plated on Chromagar supplemented with ESBL-selective antibiotics (CHROMagar) and incubated at 37 °C for 18 hours to 24 hours. Presumptive *E.*
*coli* colonies and *K. pneumoniae* colonies will be subcultured onto Columbia blood agar and further tested using biochemical methods. Antibiotic sensitivity testing will be performed using the Kirby-Bauer method, and ESBL confirmation will be conducted using the double-disk diffusion method. ESBL-producing bacteria under investigation will be subjected to whole genome sequencing to describe phylogenies as well as virulence and AMR. Data will be entered into a REDCap database, and bacteriological data will be analyzed using STATA (StataCorp). The number and percentage of samples along with descriptive statistics (ie, median, IQR, minimum, and maximum) will be reported for continuous non-normally distributed data. Categorical variables will have the number and percentage of patients reported. Proportions of positive test results will be calculated as percentages of positive results among all valid tests, with exact binomial 95% CIs.

#### Phase 1.2: Anthropology

Ethnographical studies, including daily immersions, participant observations, free discussions, and semistructured interviews, will be used. For the qualitative investigations in human health, a research assistant will be living in a community area of the rural town where the research will take place (Nouna in Burkina Faso, Agogo in Ghana) for a total of 12 months. He or she will become part of the community and, during an exploratory phase, will observe and talk to as many people as he or she meets during their daily life (neighbors; the people he or she meets when shopping, eating, and investigating places where medicines are distributed and care is provided). During the 12 months, he or she will travel to a rural locality around where he or she will live for 2 months and become integrated and that he or she will explore in the same way as previously in the town. Subsequently, he or she will conduct semistructured interviews in 15 households in the urban community and in 15 households in the rural locality (if possible, with the mother and the father). These households will have at least 1 child younger than 10 years and will be chosen to represent different socioeconomic statuses (“affluent” households, “intermediate” households, “deprived” households).

For the qualitative investigations in poultry farms, ethnography will be performed in approximately one-half of the active farms in the rural town in each country. We will choose the farms according to their operating time (from before 2000 until now) and the number of animals raised (500 to 8000 chickens).

Antibiotic use by individuals and farmers and waste management practices at the household, farm, and health care system levels will be investigated. In addition to antibiotic use, the overall living and working conditions, constraints experienced, and factors influencing health-seeking behaviors for both humans and animals will be studied. We will also explore practices of professional actors in biomedicine and veterinary medicine in addition to developing an exhaustive inventory of antibiotics in circulation. Semistructured interview guides used within the anthropology work package for the ethnographies conducted on farms and villages can be found in Multimedia Appendix 1 and Multimedia Appendix 2, respectively, and the observation guide for households in the villages for human health and animal health is shown in Multimedia Appendix 3. All other observation guides can be accessed from the corresponding author upon request. All the data will be analyzed using thematic sorting in NVivo 14, identifying redundant themes and subthemes that are relevant to understanding the social realities being studied.

#### Phase 1.3: Socioepidemiology Quantitative

A household survey about the perception of AMR and the use of antibiotics will be implemented at the community level. In Ghana, a double-stage random sampling method will be used, while in Burkina Faso, simple randomization will be used due to the availability of a Health and Demographic Surveillance System. The sample will include approximately 1000 households per country. The questionnaire will be designed using the Multi-Country Public Awareness Survey from the WHO and previous literature. It will consist of 2 sections: one for the head of the household, covering socioeconomic status, demographics, and antibiotic use in livestock and another focusing on knowledge, attitudes, and practices (KAP) related to antibiotics and AMR awareness. Participants belonging to a household will be selected randomly by the interviewer. Data collection will be conducted using tablets by two separate teams in Ghana and Burkina Faso, both of whom will undergo a 5-day training before the start of fieldwork activities.

Data will be analyzed using STATA 17. Descriptive analysis will be conducted to summarize sample characteristics using frequencies and percentages for categorical data and means with standard deviations for linear data. Socioeconomic status will be calculated using principal component analysis and classified into quintiles. KAP will be assessed by assigning points to correct responses; respondents will then be categorized into groups based on their scores. Regression analysis will be conducted for both countries to explore associations. Collinearity will be assessed to ensure the reliability of the regression models.

We will look at the circulation of antibiotics in the formal sector in the two districts analyzing the register of the district pharmacy for a period of 2 years. Subsequently, we will investigate the overall quantity of antibiotics according to antibiotic classes and the AWaRe classification. Results will be reported to the general population of the district.

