## Results

The study received funding in May 2021. Ethical approvals were granted from the various committees between November 2021 and April 2022. Renewal of the ethical approval is requested and received annually from the Kwame Nkrumah University of Science and Technology Committee on Human Research Publication and Ethics.

Data collection started in April 2022 and was completed in November 2023. For the quantitative socioepidemiology part, we conducted a cross-sectional survey among 1114 participants in Ghana and 1011 participants in Burkina Faso. These numbers were based on prior sample size calculation and reflect completed data collection as of November 2023. Qualitative components in the anthropology work package included daily immersions, participant observations, free discussions, and semistructured interviews, and semistructured interviews and focus group discussions in the socioepidemiology work package. Given the exploratory nature of these methods, participants were recruited progressively across multiple target groups, with data collection continuing until saturation was reached.

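### KAP scores are to be cut into groups before regression and no analysis of the score itself is mentioned; if the groups are modelled, information on KAP associations is lost

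*Protocol article*

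**What the plan says.** The relevant text is in the protocol article, Methods, Phase 1.3: Socioepidemiology Quantitative. On the KAP part of the questionnaire it says: "KAP will be assessed by assigning points to correct responses; respondents will then be categorized into groups based on their scores". The next sentence is: "Regression analysis will be conducted for both countries to explore associations". The outcome, the type of model and the form in which KAP enters are not given, nor are the number of groups and the cut-points.

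The same paragraph contains two related statements. One deals with another constructed variable: "Socioeconomic status will be calculated using principal component analysis and classified into quintiles". The other says that continuous data will be summarised by "means with standard deviations for linear data", without saying whether the KAP score is among them.

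On size, the plan was: "The sample will include approximately 1000 households per country". The Results section reports that "we conducted a cross-sectional survey among 1114 participants in Ghana and 1011 participants in Burkina Faso" and adds: "These numbers were based on prior sample size calculation". The inputs to that calculation are not shown.

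**The concern.** A points score orders respondents over many values. Once it is cut, two people one point apart on either side of a boundary count as different, and everyone within a group counts as the same. If that grouped variable is what the regression uses, precision falls and the size of an association depends partly on where the cuts lie.

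This is a method the article states, not a detail it leaves out. The score is built first and then replaced by groups, immediately before the modelling step. KAP is also central to the survey: it fills one of the two questionnaire sections, and the second study aim includes quantifying perceptions and use of antibiotics. The Study Setting section says that contrasting the two sites is of interest, so the KAP measure needs to carry the same meaning in both countries. According to the Results section, data collection ended in November 2023 and analysis is ongoing, so the choice directly affects current work.

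**Working it through.** The article gives no figure for information loss and no inputs to its sample-size calculation, so there is no stated number to reproduce. The check asks what grouping would cost if the groups were modelled.

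**Inputs from the document.** Achieved samples of 1114 (Ghana) and 1011 (Burkina Faso), from the Results section.

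**Assumptions.** A roughly normal score; a linear association; independent respondents, so the two-stage sampling in Ghana is ignored; two-sided 5% level. The group splits are also assumed, because none is stated.

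**Step 1: information retained.** For groups with proportions p_i bounded by normal quantiles a_i and a_(i+1), the share retained is the between-group variance of the standardised score:

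R = Σ [φ(a_i) − φ(a_(i+1))]² / p_i

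For two groups cut at c this becomes φ(c)² / [p(1 − p)].

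- Median split: φ(0)² / 0.25 = 2/π = 0.637.
- 80/20 split: φ(0.84)² / (0.8 × 0.2) = 0.490.

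| Grouping | Retained | Lost | Effective n, Ghana | Effective n, Burkina Faso |
|---|---|---|---|---|
| Quintiles | 0.897 | 10% | 999 | 907 |
| Quartiles | 0.861 | 14% | 959 | 870 |
| Three equal groups | 0.793 | 21% | 884 | 802 |
| 60/20/20 | 0.697 | 30% | 777 | 705 |
| Median split | 0.637 | 36% | 709 | 644 |
| 80/20 | 0.490 | 51% | 546 | 495 |
| 90/10 | 0.342 | 66% | 381 | 346 |

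Effective n is R times the achieved n; for example, 0.637 × 1011 = 644.

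**Step 2: power.** By the Fisher z approximation, the correlation detectable with 80% power on the score is r = tanh[(1.96 + 0.84) / √(n − 3)]. This gives 0.084 for n = 1114 and 0.088 for n = 1011. Grouping multiplies r by √R. Power for the same association then falls to about 70% (three equal groups), 61% (median split) or 50% (80/20).

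**Step 3: dependence on the cut.** Take an assumed difference of 0.2 SD between two sets of 500 respondents. Power on the score is 0.885. After a two-group cut:

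- at the median of the reference set: power 0.71, odds ratio 1.38;
- with 80% of the reference set above the cut: power 0.57, odds ratio 1.43;
- with 20% above: power 0.62, odds ratio 1.41;
- with 10% above: power 0.49, odds ratio 1.46.

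The same underlying difference therefore gives different odds ratios and quite different power.

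**Step 4: sensitivity to the model.** Under a proportional-odds model, the efficiency of k groups relative to the full ranking is 1 − Σ p_i³. This gives 0.75 (median split), 0.89 (three equal groups), 0.94 (quartiles), 0.96 (quintiles) and 0.48 (80/20). The losses are smaller for balanced groups and about the same for the 80/20 split. The direction does not change.

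**The case against.** The strongest reply is that the text never links the groups to the regression. Two adjacent sentences do not specify a model. Linear regression on the score, with groups kept for tables, is compatible with what is written. This stands, and it makes the finding conditional. It does not remove it, because the groups are the only final form of KAP described and nothing says that the score will be analysed.

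A reader might infer that the plan discards a fifth to a half of the survey's information. The document does not support that. The range requires two or three groups with no split more extreme than about 80/20, and neither is stated. Any loss is also confined to associations that use the KAP score. Demographics, antibiotic use in livestock, single items and estimated proportions are untouched.

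A reader might also infer that the cut-points will follow the data or differ by country, or that knowledge, attitudes and practices will be merged into one score. The article says none of this. It is a condensed account, and such details may sit in a fuller plan, so their absence is not an error.

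Finally, the regression is described as exploratory. No primary hypothesis or power target is given, so no stated power is shown to be undermined. Grouping for reporting is a legitimate descriptive choice. Both points are fair and limit how serious this is.

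**Conclusion.** The point holds in conditional form. The plan scores KAP and then groups it ahead of the regression, with no mention of analysing the score. If the groups enter the models, every grouping examined loses information on KAP associations, whereas modelling the score loses none. The size depends on a choice the article does not state: 10% for quintiles, 21% for three equal groups, 36% for a median split and 51% for an 80/20 split, with 66% for a 90/10 split as an extreme case. These figures rest on a roughly normal score and independent respondents. This is a worthwhile, nearly free improvement to an exploratory analysis; it does not invalidate the survey.

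**What to change.** State that the regressions use the numeric KAP score. Where KAP is the outcome, use linear regression, or proportional-odds regression if the score is skewed. Where it is an explanatory variable, enter it as a score. Keep the groups for descriptive tables only, with the same absolute cut-points in Ghana and Burkina Faso, so that the contrast between sites foreseen in the Study Setting section compares like with like. If a fuller plan already does this, one clarifying sentence is enough.

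The cost is a change of wording: the score exists as soon as the points are assigned, and no new data are needed. The downside is that a coefficient per point is slightly less easy to communicate than a good/poor contrast, which the descriptive tables would still provide.
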